### Concomitant medications

2.8

After randomization, other traditional Chinese medicines and treatment methods for treating stroke or having ABRS function should be avoided during treatment. The name, usage, and dosage of medicines that must be continued for other diseases will be recorded in the case reporting form (CRF).

### Outcome measures

2.9

#### Primary outcome

2.9.1

The primary outcome will be the disability degree (mRS score) at 6 months after onset. The mRS is widely used to assess disability in stroke patients.^[14]^ The mRS divides the disability degree into 6 grades, and the score ranges from 0 to 5. A higher mRS score indicates a more serious degree of disability.

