## Introduction

1

Stroke is the leading cause of disability-adjusted life years in neurological diseases and has become one of the top 3 fatal diseases in the world.^[1]^ Cerebral hemorrhage accounts for approximately 18% to 24% of all strokes in Asian countries, which is higher than that in Western countries.^[2]^ Cerebral hemorrhage is one of the most destructive subtypes of stroke and has high morbidity and mortality.^[3]^ The median mortality rate within 1 month was 40.4%, and the functional dependence after cerebral hemorrhage was approximately 75%.^[4]^ At the same time, it was found that hematoma enlargement was closely related to prognosis.^[5,6]^ Approximately one-third of patients with cerebral hemorrhage have hematoma growth within 24 hours.^[7,8]^ However, there is no specific treatment to prevent hematoma enlargement and promote hematoma absorption to improve the prognosis. In addition, based on the current research, it has been confirmed that neither surgical treatment nor current drug treatment is the most preferred treatment.^[9,10]^

In the face of the limitations of the treatment for cerebral hemorrhage, traditional Chinese medicine (TCM) is increasingly used to treat cerebral hemorrhage.^[11,12]^ According to the theory of traditional Chinese medicine, “abnormal flow of the blood is stasis,” so stasis occurs throughout the pathological process of cerebral hemorrhage. Therefore, the key to the treatment of cerebral hemorrhage is activating blood and removing stasis. At present, there are studies focusing on the therapeutic effect of activating blood and removing stasis, but there is still a lack of high-quality clinical research on the treatment of acute cerebral hemorrhage.

We designed a multicenter, prospective, randomized, double-blind, parallel controlled clinical trial to evaluate the optimal intervention time, efficacy and safety of the activating blood, and removing stasis method for acute cerebral hemorrhage within 24 to 72 hours after onset.

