### Data collection and management

2.11

The trial uses the CRF to collect on the day of enrollment, at 24 ± 2 hours, 48 ± 2 hours, and 72 ± 2 hours after taking the medicine, 14 ± 2 days after onset. The 2 follow-up visits were carried out at 3 months ± 7 days and 6 months ± 7 days after onset. More information about the study visits is shown in Table 1.

**Table 1 T1:** Study schedule.

		After taking the medicine				Follow-up	
Assessments	Enrollment	24 h	48 h	72 h	14 days after onset	3 months after onset	6 months after onset
Informed consent	×						
Randomization	×						
Medical history	×						
Physical examination	×				×		
General demography	×						
CT scan	×	×	×	×	×		
TCM stroke syndrome evaluation scale	×				×	×	×
NIHSS	×				×		
BI	×				×	×	×
mRS	×					×	×
Routine blood test	×				×		
Routine urine test	×				×		
Routine stool + occult blood test	×				×		
Liver and kidney function tests	×				×		
Coagulation function and D-dimer tests	×				×		
Glucose test	×				×		
Electrocardiography	×				×		
Distribution of drugs	×						
Recovery after drug use					×		
Recording of combined medications	×				×		
Recording of adverse events	×				×		
Safety assessment					×	×	
mortality					×	×	×

BI = Barthel index, mRS = modified Rankin scale, NIHSS = National Institutes of Health stroke scale, TCM = traditional Chinese medicine.

The participant's name, medical records, and data collected relating to the study will remain confidential information. Participants will be identified for the purposes of the study by initials and an assigned participant number. To ensure the security of the data, study-related information will be stored in a locked file cabinet in a safe place that cannot be accessed without permission.

To ensure the authenticity, accuracy, and completeness of the data, the quality of the data will be reviewed on site by a monitor through 100% source data verification. Errors will be submitted to the researchers for correction. After the observation course of the participant, the researcher submitted the CRF, informed consent, and medication record of the participant to the main researchers of their recruiting centers for review within 3 working days and submitted these study files to the project leader for review within 1 week.

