### Statistical analysis

2.13

Inferential statistical analyses as specified will be conducted, and all comparisons will be between the ABRS granule group and the placebo group. The statistical analyst will be blinded to the participants’ personal information and group assignment during the trial. The primary analysis will be based on the full dataset following the intention-to-treat analysis principle for all efficacy outcomes, while the secondary analysis will be based on the per protocol dataset. For the analysis of safety outcomes, a safety dataset will be used. The primary outcome will be determined by a comparison of the changes in the patients’ mRS scores between the 2 groups at 6 months after onset. The secondary outcomes will include the mortality rate, hematoma enlargement percentage, all-cause mortality rate, adverse events, TCM stroke syndrome evaluation scale score, BI, and NIHSS score. The hematoma enlargement percentage will be measured at baseline, 24, 48, and 72 hours after taking the medicine and 14 days after onset. The mortality rate, all-cause mortality rate, BI, and TCM stroke syndrome evaluation scale score will be measured at 14 days, 3 months, and 6 months after onset. The NIHSS score will be measured at 14 days after onset. The mRS score will be measured at 3 and 6 months after onset.

Missing data regarding the primary and secondary outcomes will be imputed using the last observation carried forward (LOCF) method. Independent *t* tests or Wilcoxon rank-sum tests will be used to analyze continuous outcomes. Chi-squared tests will be used to analyze categorical data. Analysis of variance or a generalized linear mixed model will be used for repeated measurement data. Regarding mortality, survival probabilities will be estimated using the Kaplan–Meier method. Two-sided 95% confidence intervals will be constructed for assessment, and a 2-sided alpha level of 0.05 will be used to indicate significance. Adjustments will be made for baseline imbalances. Descriptive statistics, including the number and percentage for categorical variables and the number, mean, standard deviation, median, minimum and maximum for continuous variables, will be provided. Listings of individual patient data will also be produced. A comprehensive statistical plan will be prepared and finalized prior to unblinding and analysis of the data.

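### The primary mRS has no grade for death and missing values are filled by LOCF, so an excess of deaths in one arm can be shrunk or lost in the primary comparison

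*Protocol article*

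**What the plan says.** All statements are in the protocol article.

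- Section 2.9.1, endpoint: "The primary outcome will be the disability degree (mRS score) at 6 months after onset".
- Section 2.9.1, scale: "The mRS divides the disability degree into 6 grades, and the score ranges from 0 to 5". No grade is given for death.
- Section 2.13, missing data: "Missing data regarding the primary and secondary outcomes will be imputed using the last observation carried forward (LOCF) method". Deaths are not excepted.
- Section 2.13, analysis set: "The primary analysis will be based on the full dataset following the intention-to-treat analysis principle for all efficacy outcomes". Patients who die therefore stay in.
- Section 2.13, comparison: "The primary outcome will be determined by a comparison of the changes in" mRS between the arms at 6 months.
- Section 2.13, timing: "The mRS score will be measured at 3 and 6 months after onset". Table 1 adds an enrollment score and shows no mRS at day 14. Section 2.11 confirms the later visits: "The 2 follow-up visits were carried out at 3 months ± 7 days and 6 months ± 7 days after onset".
- Sections 2.9.2 and 2.13 list mortality and all-cause mortality as separate secondary outcomes, recorded at 14 days, 3 months and 6 months, with Kaplan–Meier estimates.

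**The concern.** Cerebral hemorrhage is often fatal, and the Introduction itself says so: "The median mortality rate within 1 month was 40.4" percent. The trial's objective covers safety as well as efficacy, and the Discussion cites earlier trials of the same treatment approach, given within 6 hours, that found no benefit and more hematoma enlargement. The primary outcome should therefore register death as a bad result.

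Under the stated rules it need not. A patient who dies has no 6-month mRS, and the only rule for an absent value is to carry the last one forward. An early death is then scored as a patient who neither improved nor worsened. The same rule gives a survivor lost before 3 months a score taken 24 to 72 hours after onset, which denies any recovery. In both cases the primary estimate rests on a value that does not describe the patient at 6 months.

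**Working it through.** **1. What the rules produce**

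| Patient | Last mRS available | 6-month value under LOCF | Change |
|---|---|---|---|
| Dies before 3 months | enrollment | enrollment score | 0 |
| Dies between 3 and 6 months | 3 months | 3-month score | as at 3 months |
| Survivor worse by one grade | 6 months | observed | +1 |
| Survivor lost before 3 months | enrollment | enrollment score | 0 |

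Higher scores are worse, so the early death ranks better than the survivor who worsens by one grade.

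**2. The plan's own figure**

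Section 2.12 gives 129 per group for 56% vs 36% unfavorable. Power is not stated there; 90% reproduces the figure. With the mean rate 0.46 and two-sided alpha 0.05:

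n = [1.96·√(2·0.46·0.54) + 1.2816·√(0.56·0.44 + 0.36·0.64)]² / 0.20² = 128.4, rounded up to 129.

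The planned 312 patients give 156 per arm, used below.

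**3. Deaths, mean mRS (illustration)**

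The article gives no trial mortality and no distribution of scores. Assumed: enrollment mRS 3/4/5 in 15/50/35%; deaths 25% vs 15%, all before 3 months; identical survivors in both arms, with 6-month mRS 0 to 5 in 8/17/20/20/22/13%.

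- Enrollment mean = 3·0.15 + 4·0.50 + 5·0.35 = 4.20.
- Survivor mean = 0.17 + 0.40 + 0.60 + 0.88 + 0.65 = 2.70.
- Death scored 6: difference = (0.25 − 0.15)·(6 − 2.70) = 0.33.
- LOCF: difference = (0.25 − 0.15)·(4.20 − 2.70) = 0.15.

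The loss, 0.10·(6 − 4.20) = 0.18, does not depend on survivor recovery. The detection rate does. In 4,000 simulated trials with these inputs, a rank-sum test on the final score found the harm in 33% with death scored 6 and 14% under LOCF; on the change score, 30% and 15%. With other survivor patterns, detection with death scored 6 stayed between about 33% and 37% on the final score. Under LOCF it was 10 to 19% on the final score and 14 to 27% on the change score. In round terms, detection goes from one third to one fifth or less on the final score.

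**4. Deaths, binary outcome (illustration)**

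Assume a 56% control rate with death counted as unfavorable, deaths 20% (placebo) vs 30% (ABRS), and identical survivors. The unfavorable rate among survivors is (0.56 − 0.20)/0.80 = 0.45, so the ABRS rate is 0.30 + 0.70·0.45 = 0.615. The true difference is 5.5 points. If a share f of the carried scores is favorable, the LOCF difference is 5.5 points less 10·f:

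- f = 0: 5.5 points, no distortion.
- f = 25%: 3.0 points.
- f = 50%: 0.5 points.

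**5. Survivors lost to follow-up (worst case)**

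Assume the whole 20% dropout leaves before 3 months with an unfavorable enrollment score:

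- 0.8·0.56 + 0.2 = 0.648 and 0.8·0.36 + 0.2 = 0.488.
- Power at 156 per arm, mean rate 0.568: Φ[(0.16·√156 − 1.96·√(2·0.568·0.432)) / √(0.648·0.352 + 0.488·0.512)] = Φ(0.90) = 0.817.
- Completers alone, 124.8 per arm at 56% vs 36%: 0.892.

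With 10% lost in this way, the rates are 60.4% vs 42.4% and power is 0.893, against 0.924 in completers.

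**The case against.** The strongest reply is that the article never says death is missing data. It treats death as an outcome of its own and promises a full statistical plan before unblinding, where the coding of deaths could be settled. This lowers certainty about what the analysts will do. It does not remove the point: the article fixes both the 0 to 5 scale and LOCF and gives no other rule. A plan that follows them inherits the problem, and one that departs from them contradicts the published protocol.

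Three stronger readings are tempting, and the document does not support them.

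- *A reader might infer that differences in death would be hidden from the trial.* They would not. Mortality is a secondary outcome with Kaplan–Meier estimates. At 25% vs 15% and 156 per arm, a two-sided Z test of mortality has power Φ[(0.10·√156 − 1.96·√(2·0.20·0.80)) / √(0.25·0.75 + 0.15·0.85)] = Φ(0.25), about 60%. That is more than the one third for mRS with death scored 6. The defect lies in the primary result.
- *A reader might apply the 40.4% one-month mortality to this trial.* It describes cerebral hemorrhage in general. Enrollment at 24 to 72 hours, a Glasgow score above 6, and the exclusion of coma, hernia and emergency surgery make it an upper bound at most. The cited harm signal concerns treatment within 6 hours and hematoma enlargement, not death.
- *A reader might assume the same distortion in any analysis.* The sample size uses a binary unfavorable rate. Many acute scores would already be unfavorable, so many early deaths would be classified correctly. The distortion is largest in the comparison of changes that section 2.13 names.

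The sizes above also rest on assumed inputs, and the survivor calculation is an extreme.

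**Conclusion.** The point stands for the primary outcome. Applied as written, the 0 to 5 scale, LOCF without an exception for death, and an mRS schedule with nothing between enrollment and 3 months score an early death as no change, and a later death at its 3-month grade. This can shrink or remove an excess of deaths in the primary comparison of mRS changes.

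In the example, 0.18 of a true mean difference of 0.33 is lost. That figure depends on the assumed enrollment mean of 4.20 and the 10-point excess of deaths; the fall in detection also depends on survivor recovery. None of these is given in the document, so the numbers show direction and plausible scale, not a prediction. For survivors, the dilution to 64.8% vs 48.8% with power of about 82% is a worst case.

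The matter should be settled before unblinding, because it affects the primary estimate and the remedy needs no new data.

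**What to change.** Amend sections 2.9.1 and 2.13 before unblinding:

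1. Define the primary outcome on mRS 0 to 6, with death by 6 months scored 6 and counted as unfavorable in any dichotomy. Take it from the vital status already recorded at 14 days, 3 months and 6 months, and do not impute it.
2. For survivors with a missing 6-month score, do not carry the enrollment mRS forward. Use multiple imputation or a likelihood-based model with the enrollment, day-14 (NIHSS, BI) and 3-month data.
3. Add a sensitivity analysis in which a missing outcome counts as unfavorable.

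The cost is a change of wording and slightly more analysis work. No visit, measurement or patient is added.

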### Sample size

2.12

The sample size was calculated by PASS software version 15 (Kaysville, UT). In a previous study, the rate of unfavorable disability (according to the mRS score) in the control group was 56%.^[15]^ We assume that the rate of unfavorable disability (according to the mRS score) in the treatment group will be 36%, that is, decreased by 20%. After a 2-sided Z test, PASS software calculated that the sample size of each group should be 129. Considering a 20% dropout rate, 312 patients will need to be enrolled.

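### The primary mRS has no grade for death, and the only written rule for an absent 6-month score (LOCF) would understate a mortality difference in the primary result

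*Protocol article*

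**What the plan says.** - **Endpoint (2.9.1):** "The primary outcome will be the disability degree (mRS score) at 6 months after onset". The scale is then fixed: "The mRS divides the disability degree into 6 grades, and the score ranges from 0 to 5". Death has no grade.
- **Comparison (2.13), with time counted from onset:** "The primary outcome will be determined by a comparison of the changes in the patients’ mRS scores between the 2 groups at 6 months after".
- **Analysis set (2.13):** "The primary analysis will be based on the full dataset following the intention-to-treat analysis principle for all efficacy outcomes".
- **Absent data (2.13):** "Missing data regarding the primary and secondary outcomes will be imputed using the last observation carried forward (LOCF) method". No exception is made for death.
- **Timing (2.13):** "The mRS score will be measured at 3 and 6 months after onset". Table 1 adds an mRS at enrollment and none at 14 days.
- **Death elsewhere:** mortality and all-cause mortality are secondary outcomes at 14 days, 3 months and 6 months, with Kaplan–Meier estimates (2.9.2, 2.13, Table 1).
- **Planning (2.12):** in an earlier study "the rate of unfavorable disability (according to the mRS score) in the control group was 56"%, and 36% is assumed on treatment. Whether either rate counts deaths is not said.

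**The concern.** Taken together, these statements leave one written route for a patient who dies before the 6-month visit. The scale offers no value for death, the intention-to-treat set keeps the patient in, and LOCF supplies the last score taken while the patient was alive.

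For a death before the 3-month visit, that score is the enrollment mRS, so the recorded change is 0. A survivor who goes from 4 to 5 has a change of +1 and ranks worse than that death. For a death between 3 and 6 months, the 3-month score stands, even if it was a good one.

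At stake is what the main efficacy result means. If ABRS granules raise or lower mortality, the primary comparison shows only part of the effect, and a reader of that result alone would be misled about its size.

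**Working it through.** **1. The plan's own figure.** Inputs from 2.12 and 2.13: 56% v 36%, two-sided alpha 0.05. Power is not stated; 90% is assumed because it reproduces the result. With the pooled Z test and mean rate 0.46:

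n = [1.960 × √(2 × 0.46 × 0.54) + 1.282 × √(0.56 × 0.44 + 0.36 × 0.64)]² / 0.20² = (1.381 + 0.885)² / 0.04 ≈ 128.4, so 129 per group.

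This matches the article. It depends on what counts as unfavorable, which is why the place of death matters here too. The total of 312 gives 156 per arm.

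**2. What LOCF has to carry.**

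| Time of death | mRS available | Scored change from enrollment |
|---|---|---|
| Before 3 months | enrollment only | 0 |
| 3 to 6 months | enrollment, 3 months | 3-month score minus enrollment score |

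**3. Effect on the mean, under assumptions.** The article gives no mortality or mRS distribution for this trial, so the following are assumed:
- enrollment mRS 2/3/4/5 in 5/15/45/35%;
- 6-month mRS 0 to 5 in survivors of 8/20/20/22/20/10%, the same in both arms;
- death more likely with a higher enrollment score;
- 75% of deaths before 3 months.

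Survivor mean = 0.20 + 0.40 + 0.66 + 0.80 + 0.50 = 2.56. Enrollment mean = 0.10 + 0.45 + 1.80 + 1.75 = 4.10.

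- With death = 6, the mean difference is (difference in death rate) × (6 − 2.56). At 15% v 30% this is 0.15 × 3.44 = 0.52; at 10% v 20% it is 0.10 × 3.44 = 0.34.
- Under LOCF, an early death has change 0 while the average survivor has 2.56 − 4.10 = −1.54. The gap is 1.54 instead of 3.44, a ratio of 0.45. The effect is therefore roughly halved, not removed.

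**4. Simulation under the same assumptions** (156 per arm, Wilcoxon test at two-sided 0.05). Ranges are across repeated runs, including different weights for how death depends on the enrollment score.

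| Deaths | Mean difference, death = 6 | Mean difference, LOCF | Detection, death = 6 | Detection, LOCF |
|---|---|---|---|---|
| 15% v 30% | 0.52 | 0.22–0.26 | about 65% | 22–32% |
| 10% v 20% | 0.34 | 0.15–0.17 | about 35% | 14–17% |
| 5% v 10% | 0.05 × 3.44 = 0.17 | not tabulated | 12–14% | 6–9% |

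A second set of assumptions gives the same picture: 129 per arm, survivors 8/16/20/18/22/16%, and last living scores all 4 or 5, or 30% at 2. At 10% v 20% deaths the difference falls from 0.31–0.32 to 0.10–0.16, and detection from 27–30% to 8–15%.

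**5. Two readings that change the size.**
- *Binary endpoint.* Section 2.12 plans on an unfavorable rate. Taking mRS 3 or more as unfavorable (an assumption), 15 + 45 + 35 = 95% of enrollment scores are already unfavorable, so most early deaths still count as such under LOCF. At 15% v 30% deaths, detection falls from 26% to 16–23%; at 10% v 20%, from 14% to about 10% in one run. If every carried score is 4 or 5, nothing is lost.
- *Enrollment mRS is the pre-onset score.* Section 2.3.1 requires a pre-onset score of 0 to 1, and Table 1 does not say which score is taken at enrollment. If it is the pre-onset one, an early death is carried at 0 or 1, while the average survivor has worsened by between 2.56 − 1 = 1.56 and 2.56 − 0 = 2.56. Excess deaths then look like benefit. One run at 15% v 30% gave −0.22, with about 26% of trials significant.

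**The case against.** **The LOCF step is an inference.** This stands in part. Section 2.13 speaks of missing data and never calls death missing, and it defers detail to a statistical plan that is not shown. A reader might infer that the article orders LOCF for the dead; it does not say so. But it fixes the range and the imputation rule. A later plan that scored death as 6 would contradict 2.9.1, and one that exempted deaths from LOCF would narrow 2.13.

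**Deaths are reported anyway.** This stands. Two mortality outcomes are planned, and serious adverse events go to the ethics committee within 24 hours (2.10). A reader might infer that the trial hides deaths; it does not. The defect is confined to the primary result.

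**High mortality may not apply.** This stands. The Introduction says "The median mortality rate within 1 month was 40.4"%, but that is background. This trial enrolls at 24 to 72 hours, requires a Glasgow score above 6, and excludes coma, herniation and emergency surgery. The figure should not be used as the trial's death rate.

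**Earlier harm in the Discussion.** A reader might infer a known mortality risk from it. The text concerns treatment within 6 hours and reports lack of benefit and hematoma enlargement, not death, and it calls the overall trend favorable. It does not support a mortality claim for this trial.

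**Deaths might simply be excluded.** Nothing in the article says so, and the intention-to-treat statement speaks against it.

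**Conclusion.** The point holds as an error in what is written: a 0 to 5 scale, LOCF without exception and an intention-to-treat set leave no route by which death ranks worst in the primary outcome. The primary result would understate a mortality difference in either direction.

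The size cannot be fixed from the documents. With arms that differ only in mortality, by 10 to 15 percentage points, about half of the mean difference is lost and detection falls by half or more. With 5% v 10% deaths there is little power under either rule and the loss is small. On a binary endpoint it is also smaller, and can be nil. It is worse, with a possible reversal of sign, if the enrollment mRS is the pre-onset score. The stronger reading, that the primary result conceals deaths entirely or turns them into benefit, is not supported unless that last reading applies.

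**What to change.** - **2.9.1:** define the primary mRS as 0 to 6, with death = 6, and name the outcome disability or death.
- **2.13:** state that a patient known to have died by 6 months is scored 6 and that LOCF never applies to the dead. The death = 6 figures above compare the 6-month score itself, as 2.9.1 defines it. If change scores are kept, a death from an enrollment score of 5 is only 6 − 5 = +1, so the text should also say that death takes the worst rank.
- **2.12:** state that death counts as unfavorable and confirm whether the cited 56% includes deaths. If it does not, restate both planning rates and recalculate the 129 per group.
- **Table 1:** say whether the enrollment mRS is the current or the pre-onset score.

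The cost is wording, as death is already recorded at 14 days, 3 months and 6 months, plus a possible sample size recalculation. The downside is that the primary outcome is no longer disability alone; survivor-only mRS can be shown descriptively. The change should be made before unblinding.
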